### Participants and setting

Participants will be PWD living in 22 nursing homes of the Canton Ticino area, Switzerland. Participants will meet the following inclusion criteria: presence of moderate to severe dementia, assessed using the Global Deterioration Scale (GDS 4–7) [26]; presence of at least one BPSD in addition to depression or apathy assessed with the NPI-NH; female gender; admission in the nursing home at least 3 months before; and no previous DT exposure. The exclusion criteria were the following: male gender; presence of comorbid mental disorders, such as major depression, bipolar disorders and schizophrenia; inability to sit comfortably on a chair or limitations in mobility of the arms; or presence of acute clinical conditions interfering with the participation to the study.

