### Sample size

To our knowledge, at the start of the study on 1 February 2017, no previous study had measured the efficacy of DT using the NPI-NH score. Therefore, a referral upon existing data could not be used in the power calculation. The power analysis was conducted using an estimated medium effect size (*f* = 0.25), an alpha level of 0.05, and a power of 0.8. According to statistical computing, a sample size of *n* = 128 is required, with 64 participants per group, for an analysis of covariance that includes the NPI-NH baseline score as a covariate. We planned an increase in sample size of 13 participants, because the expected drop-out rate is 10% due to possible acute clinical conditions interfering with the participation in the study, or death. In case of a refusal of the object (doll or cube), another participant will be enrolled as a replacement. Participants who underwent less than 60% of sessions will be excluded from analysis. The power calculation was performed with the programme *G*Power* 3.1 [27].

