## Measurements

### Primary outcomes

#### Behavioural outcome

The primary outcome is the decrease of the patient’s BPSD measured as the net change in the NPI-NH total score from baseline to post intervention. We expect a significant difference in NPI-NH total scores between the experimental and active control groups. The NPI-NH has been specifically designed for interviewing professional care facility staff; it has been validated in different countries, and the Italian version of the scale has demonstrated good psychometric properties [22]. It will be administered to the staff by a trained blinded psychologist. The time frame of that evaluation is from baseline (T0) to 30 days after the beginning of the intervention (T2).

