### Statistical analyses

As a first step, a post hoc evaluation by descriptive statistical comparisons between the intervention and the control groups in age and baseline NPI-NH will be conducted to assess the effectiveness of the randomised assignment. To evaluate associations between biological parameters (decreased, influent, or increased) of each patient at the baseline versus the post intervention, the chi-square test or Fisher’s exact test will be performed. Primary outcomes will be tested performing an analysis of covariance (ANCOVA) of these measurements with the experimental group as the factor baseline NPI-NH and total number and posology of psychopharmacological therapies as the covariates. In order to evaluate how much variance in NPI-NH net change can be explained by groups (experimental versus control groups) after controlling for baseline NPI-NH and biological parameters, a multiple regression analysis will be performed.

Treatment efficacy will be analysed by a per-protocol analysis (PPA) that excludes all drop-outs. Differences will be considered statistically significant when *p* values are lower than 0.05.

All analyses will be conducted using Stata version 13 (Stata Corp., College Station, TX, USA).

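### The ANCOVA of NPI-NH and NPI-NH-D has no nursing-home term; a random home intercept would recover a modest, ICC-dependent amount of power at almost no cost

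*Protocol article*

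**What the plan says.** Under Statistical analyses, the primary outcomes are to be tested by an ANCOVA "with the experimental group as the factor baseline NPI-NH and total number and posology of psychopharmacological therapies as the covariates". The multiple regression described next in that section has no home term either. The sample size section powers the trial "for an analysis of covariance that includes the NPI-NH baseline score as a covariate", with no allowance for home.

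On the setting, the article states "Participants will be PWD living in 22 nursing homes of the Canton Ticino area, Switzerland". On how NPI-NH is obtained, Behavioural outcome says "It will be administered to the staff by a trained blinded psychologist", and the section on professional caregiver distress says the same of NPI-NH-D. Description of interventions has the sessions led by a trained professional caregiver and held in the residence. Randomisation and blinding describes individual 1:1 allocation in blocks of four and does not mention stratification by home.

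**The concern.** Residents of one home live under the same care and are rated from reports by that home's staff. Their scores are therefore likely to be more alike than those of residents of different homes, even after adjustment for baseline. In an individually randomised trial, an analysis that ignores home leaves this between-home variation in the error term. A model with a home term can remove part of it. What is at stake is precision: the plan has almost no slack above 80% power, its effect size is conventional, and home is known for every participant at no extra effort.

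**Working it through.** **Inputs from the article.** Effect size, alpha and power: "The power analysis was conducted using an estimated medium effect size (*f* = 0.25), an alpha level of 0.05, and a power of 0.8". Sample size: "a sample size of *n* = 128 is required, with 64 participants per group". Homes: 22. Planned enrolment: 128 + 13 = 141.

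**Input that is assumed.** The residual ICC by home, after baseline adjustment, is not given. The range used is 0 to 0.20.

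**Step 1: residents per home.** 128/22 = 5.8 analysed and 141/22 = 6.4 enrolled, so about six on average. The article does not give the distribution across homes.

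**Step 2: the plan's own figure.** For two equal groups, f = 0.25 corresponds to d = 0.5. The noncentrality is λ = f² × N = 0.0625 × 128 = 8. With 1 numerator df and 128 − 2 − 1 = 125 denominator df, the noncentral F gives power 0.801. N = 128 is reproduced, and it stays at 128 with three covariates.

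**Step 3: upper bound on the gain.** Take f in units of the total residual SD, which is the error SD of a model without home. Ignoring home then leaves power at 0.801 at every ICC. If all between-home variance were removed at no cost, λ would become 8/(1 − ICC):
- ICC 0.05: λ = 8.42, power 0.821
- ICC 0.10: λ = 8.89, power 0.841
- ICC 0.20: λ = 10.0, power 0.881

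**Step 4: realistic gain by simulation.** N = 128 in 22 homes, d = 0.5, central blocks of four unrelated to home, 4,000 runs per row. The Monte Carlo SE of a power figure is √(0.8 × 0.2/4000) = 0.6 points. The models are compared on the same simulated data. Figures are power in %, with gains taken before rounding.

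| Home sizes | ICC | No home term | Random intercept | Gain (points) | 22 fixed effects |
|---|---|---|---|---|---|
| 5–6 each | 0 | 79.8 | 80.2 | 0.4 | 72.3 |
| 5–6 each | 0.05 | 80.3 | 80.5 | 0.2 | 74.3 |
| 5–6 each | 0.10 | 80.6 | 82.1 | 1.5 | 78.4 |
| 5–6 each | 0.20 | 79.8 | 84.4 | 4.7 | 81.1 |
| 1–14 each | 0 | 79.0 | 79.1 | 0.1 | 71.5 |
| 1–14 each | 0.05 | 80.5 | 81.1 | 0.5 | 75.2 |
| 1–14 each | 0.10 | 79.4 | 81.0 | 1.7 | 76.3 |
| 1–14 each | 0.20 | 79.5 | 84.4 | 4.9 | 80.9 |

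A separate simulation of the same design gave paired powers of 0.805/0.809, 0.810/0.817 and 0.798/0.843 at ICC 0.05, 0.10 and 0.20. Those are gains of 0.4, 0.7 and 4.5 points.

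**Step 5: type I error, same design.** Without a home term it was 4.9% to 5.3%; with the random intercept, 4.6% to 5.5%. Both are near nominal.

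**Step 6: if blocks were applied within home.** At ICC 0.20 the test that ignores home rejected a true null in 3.7% (equal sizes) and 3.4% (unequal sizes) of runs, so it is conservative. Its power was 82.7%, against about 87% with the random intercept. The gain from the random intercept was about 1, 2 and 4 to 5 points at ICC 0.05, 0.10 and 0.20.

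**Step 7: why not fixed effects.** When allocation is not balanced within home, 22 home effects absorb part of the treatment contrast. The noncentrality at ICC 0 falls to about 8 × 106/127 = 6.68 on 128 − 2 − 3 − 21 = 102 df, giving power 0.726. This agrees with the simulated 72%.

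**The case against.** The strongest reply is that nothing is wrong with the plan as it stands. The ANCOVA is valid under individual randomisation, it matches the model behind the sample size apart from the drug covariates, and it delivers the planned 80%. That stands, and it limits the point to an optional gain in efficiency.

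The gain also rests wholly on an assumed ICC. Baseline NPI-NH is collected by the same procedure, so a lenient or strict rating habit that persists in a home is partly removed by that covariate, and the residual ICC could be small. That stands too: up to ICC 0.10 the gain is at most about 2 points.

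It may be said that a condensed article leaves such detail to the full protocol or analysis plan. This stands for stratification, on which the article is silent. It does not stand for the model, whose terms the article lists.

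Several stronger readings are tempting but not supported:
- **Inflated false positives, or a cluster-trial design effect.** Residents, not homes, are randomised, and the simulated type I error is near 5%. Session leaders who each served only one arm would be a different problem, but the article does not describe that.
- **An underpowered trial.** Ignoring home leaves power at about 80% at every ICC examined.
- **Informants known to be shared, or to be the session leaders.** The article does not say how many residents one staff member rates or serves, or whether the roles overlap.
- **NPI-NH-D as the most affected outcome.** This is plausible for a rating of staff distress, but no figure in the article shows it.
- **An omission without any advantage.** The plain model is simpler, and it beats fixed home effects when the ICC is low.

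**Conclusion.** The point holds as a low-severity improvement. The stated ANCOVA omits a known grouping factor that probably carries some outcome variation. Under individual randomisation with blocks not tied to home, the cost is a forgone gain: about 0 to 1 point of power at a residual ICC of 0.05, 1 to 2 points at 0.10 and 4 to 5 points at 0.20. If blocks were applied within home, the gain is of similar size and the unadjusted test is also conservative, at about 3.5% for ICC 0.20.

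These sizes assume d = 0.5 in total residual SD units, 128 analysed residents in 22 homes, and an ICC range that the article neither gives nor rules out.

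**What to change.** Fit the ANCOVA of NPI-NH and of NPI-NH-D as a linear mixed model with a random intercept for nursing home, keeping arm, baseline NPI-NH and the psychopharmacological covariates as they are. Do not enter the 22 homes as fixed effects. State in the same place whether the blocks of four were applied centrally or within home.

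The change takes about one line in the analysis section, needs no new data, and showed no loss of power at ICC 0. Its downside is slight added model complexity, mainly where homes contribute few residents.

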### Other variables

Other variables will be collected for the purpose of the present study, as follows: age of the PWD at the time of baseline; baseline Mini Mental State Examination (MMSE) score [34]; total number and relative dosages of psychopharmacological therapies for behavioural and psychiatric symptoms; presence of physical restraints; number of children and monthly visits to the PWD; age and gender of the offspring of PWD. A summary of the assessment performed at each time of the study is reported in Table 3.

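### The primary ANCOVA has no dementia-severity term, although every participant is staged on the GDS at entry: a possible, unquantified loss of precision that can be avoided at almost no cost

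*Protocol article*

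**What the plan says.** All references are to the protocol article.

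- **Statistical analyses** sets one model for all primary outcomes. Its terms are listed as follows: "with the experimental group as the factor baseline NPI-NH and total number and posology of psychopharmacological therapies as the covariates". A separate multiple regression of NPI-NH change controls for baseline NPI-NH and biological parameters. The descriptive check of the randomisation compares the groups "in age and baseline NPI-NH will be conducted to assess the effectiveness of the randomised assignment". Efficacy is analysed per protocol, without drop-outs.
- **Participants and setting** requires "presence of moderate to severe dementia, assessed using the Global Deterioration Scale (GDS 4–7").
- **Other variables** lists "baseline Mini Mental State Examination (MMSE) score" among the data collected and gives it no role in any analysis.
- **Sample size** plans 64 per group "for an analysis of covariance that includes the NPI-NH baseline score as a covariate". Participants who refuse the object are replaced, and those with less than 60% of sessions are left out of the analysis.
- **Randomisation and blinding** describes 1:1 allocation in blocks of four and names no stratification factor.

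Neither GDS nor MMSE appears in the ANCOVA, the regression or the stated balance check.

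**The concern.** The entry range runs over four GDS stages. Stage could plausibly be related to behavioural symptoms and to how a person handles an object. If it predicts an outcome beyond what baseline NPI-NH and psychotropic treatment already explain, leaving it out keeps that variation in the error term and widens the confidence interval for the group difference.

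The second exposure is imbalance. Nothing stated in the article balances, checks or adjusts for severity. In the full randomised set an imbalance could arise only by chance. The set analysed is smaller than that: refusers are replaced, low attenders are excluded and drop-outs are removed. If acceptance of a doll and acceptance of a cube depend differently on stage, the analysed arms could differ in severity for reasons other than chance. The article gives no data on whether they do.

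The covariate list is written out in the article, so this concerns a choice that the document makes, not a detail left to a fuller plan.

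**Working it through.** **1. Inputs from Sample size.** f = 0.25, "an alpha level of 0.05, and a power of 0.8", N = 128 in two equal groups. For two equal groups f = 0.25 corresponds to d = 2 × 0.25 = 0.50.

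**2. Reproducing the stated N.** Noncentral F with λ = N·f², df1 = 1, df2 = N − 2 − (number of covariates).

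λ = 128 × 0.0625 = 8. With one covariate (baseline NPI-NH), df2 = 125 and power is 0.8014. At N = 126 power falls below 0.80, so 128 is the smallest even total. The stated figure reproduces and does not rely on severity.

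**3. Cost if severity is uninformative.** I count the planned model as three covariates (baseline NPI-NH, number of drugs, posology).

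| Covariates | Power at N = 128 |
|---|---|
| 3 (as planned) | 0.8013 |
| 4 (GDS added as one linear term) | 0.8013 |
| 6 (GDS added as four categories) | 0.8012 |

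**4. Gain if severity is informative.** Let R² be the share of residual variance that severity explains once the planned covariates are in the model. The article gives no such figure, so the values below are assumptions. Then λ = 8/(1 − R²), and the standard error of the group difference is multiplied by √(1 − R²). Four covariates, N = 128:

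| Assumed R² | λ | Power | SE multiplier | N for 80% power |
|---|---|---|---|---|
| 0 | 8.00 | 0.8013 | 1.000 | 128 |
| 0.05 | 8.42 | 0.8210 | 0.975 | 122 |
| 0.10 | 8.89 | 0.8408 | 0.949 | 116 |
| 0.20 | 10.00 | 0.8805 | 0.894 | 104 |

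The gain passes two power points only when R² is above about 0.05.

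**5. What a chance imbalance could do in one trial.** With 64 per arm, the standardised difference in mean severity has SD √(2/64) = 0.177. In 5% of trials it exceeds 1.96 × 0.177 = 0.35 SD in one direction or the other. The unadjusted estimate then shifts by √R² × 0.35 residual SD. Set against d = 0.50:

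- R² = 0.05: 0.08 residual SD, about 15% of the planned effect
- R² = 0.10: 0.11, about 22%
- R² = 0.20: 0.15, about 31%

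These shifts average to zero over randomisations. They describe an unlucky single trial and are not a bias of the design. No figure can be put on imbalance created by the per-protocol exclusions, because the article gives no exclusion rates by arm or stage.

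**The case against.** The strongest objection is that this is a preference between two reasonable covariate sets. The plan already adjusts for the baseline of its main behavioural outcome, the sample size is correct on that basis, and under randomisation omitting a prognostic factor from a linear model biases neither the estimate nor the test. All of that stands for the randomised set. It carries less weight for the per-protocol set, which is the set analysed, and it gives no reason to leave out a variable that is obtained anyway and costs almost nothing to include.

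Five stronger readings are tempting, and the documents do not support them:

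- *Explainable variation certainly remains in every primary outcome.* No section gives a correlation between severity and any outcome, and for NPI-NH the baseline score may already carry much of it. Many items of the interaction grid are present/absent, so an ANCOVA error term does not describe them. The recorded durations are a different matter.
- *The article itself says that outcome depends on stage.* The Background suggests only tentatively that attachment theory might explain how the doll works in advanced dementia. That concerns mechanism and target population. If it did imply a dependence on stage, it would point to effect modification, which a main-effect covariate does not address.
- *Drop-out leaves the trial short, which makes the loss worse.* The plan adds 13 to 128, and 90% of 141 is about 127.
- *Severity imbalance will go unreported.* The article names only age and baseline NPI-NH, but it is a condensed account, and a full baseline table may exist elsewhere.
- *GDS stage is certainly in the database.* It must be assessed for eligibility, but Other variables does not list it and the content of the schedule table is not shown. That the stage itself is kept, and not only a pass or fail, is an assumption.

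**Conclusion.** The point holds as a low-cost improvement. The stated ANCOVA has no severity term in a trial that admits GDS 4 to 7 and must stage every participant. The stated sample size and the type I error rate are not affected. The possible cost is precision: nothing if severity adds no information, about 2 power points at an assumed residual R² of 0.05, about 4 at 0.10 and about 8 at 0.20. The documents cannot settle which applies. There is also exposure to severity imbalance in the per-protocol set, of unknown size.

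The power figures assume f = 0.25, 128 analysed and a linear model for a continuous outcome. They do not carry over to the present/absent items.

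**What to change.** In Statistical analyses, pre-specify baseline GDS stage as one additional covariate in the ANCOVA of the continuous primary outcomes, alongside baseline NPI-NH and the psychotropic variables. Add GDS stage by arm to the descriptive baseline comparison, and confirm that the stage found at screening is kept in the data. Do not rely on MMSE if it is missing for the most impaired participants, because a complete-case model would then lose exactly those women.

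State the expected gain as unknown, and leave the sample size as it is. Adjusting for GDS does not repair the per-protocol exclusions; it gives partial protection, and the table by arm makes any imbalance visible.

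The cost is one sentence and about one degree of freedom (three if stage is entered as categories), with power at N = 128 lower by less than 0.001 if severity proves uninformative. The article reports that recruitment was still under way, so the change should be dated before any outcome is compared between arms; made later, it would look data-driven.

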## Background

Doll therapy (DT) is a non-pharmacological intervention to support people with dementia (PWD) and is recommended for the treatment of behavioural and psychological symptoms of dementia (BPSD) [1]. Previous literature provided some direction on how to use dolls as a nursing instrument [2–6]. Observational studies have shown the benefits of DT in reducing BPSD such as agitation, aggression and wandering [7, 8]. They have also shown the benefits of DTS in increasing communication between patients and caregivers due to the fact that dolls stimulate conversation on topics related to motherhood and caregiving [9, 10]. A significant reduction of antipsychotic drug dosage (e.g. haloperidol) has also been reported [11]. Furthermore, the benefits provided from DT fulfil the bioethics’ concepts of beneficence (facilitates the promotion of well-being) and respect for autonomy (PWD can exercise their right to engage with dolls if they wish) [12]. Despite promising results, available studies on the efficacy of dolls’ use are mainly pilot or exploratory studies [13–15]. Randomised controlled trials are needed in order to support the clinical efficacy of DT in managing BPSD and reducing professional caregivers’ perceived stress linked to BPSD. Moreover, empirical research is needed to identify best practice for DT interventions for PWD because there are differences among approaches to the practice being advocated. There are also difficulties in standardising the design and delivery of such complex interventions [16].

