## Methods/design

### Primary goal

The primary goal of the present study is the 30-day efficacy of the Doll Therapy Intervention (DTI) versus a Sham Intervention (SI) on BPSD, professional caregivers’ perceived stress, patients’ physiological indices of stress, and interactive behaviours of PWD living in a nursing home. In particular, we expect an improvement in terms of a decrease in the Italian version of the Neuropsychiatric Inventory-Nursing Home total score (NPI-NH) [22, 23]. We also expect an improvement of professional caregivers’ perceived stress linked to BPSD of PWD in terms of a decrease in the NPI-NH Distress (NPI-NH-D) total score. Furthermore, we expect an improvement of the patients’ physiological indices of stress linked to their BPSD in terms of a decrease in the following parameters: salivary cortisol, blood pressure (systolic and diastolic) and heart rate, which are well-known biomarkers of acute stress. Finally, we expect an improvement of the patients’ interactive behaviours towards the object (doll) in terms of an increase in the number and duration of exploratory and caregiving behaviours.

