#### Physiological outcomes

We have planned to monitor three physiological outcomes: blood pressure (systolic and diastolic), heart rate and salivary cortisol level. Blood pressure (systolic and diastolic) and heart rate are biomarkers of acute stress involved in the response to physical and psychosocial stressors. Salivary cortisol level is a biomarker of stress, and its secretion is the final product of the activation of stress-response mechanisms; specifically, the hypothalamic-pituitary-adrenal axis [29]. Changes in its secretion rate were reported during acute responses to stress in the context of illnesses and in cognitive impairment [30], in mood disorders [31] and in individuals with different adult attachment styles [32]. Professional caregivers will collect the saliva samples, blood pressure (systolic and diastolic) and heart rate readings of each participant in both the experimental and control groups, immediately before the treatment and 15 min after the end of treatment at the first and the 30th session of DTI or SI. We expect a significant difference between the experimental and the control group in blood pressure levels and heart rate from the first to the 30th session. A ratio between pre-treatment versus ‘after 15 min’ will be calculated for the first and 30th sessions. We expect a significant difference in the concentration of salivary cortisol between the experimental and control groups from the first to the 30th sessions.

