The attachment styles are recognised as being persistent during the ageing phases as demonstrated by previous studies based on the AAI, but the PWD cannot be interviewed. To date, there are no studies which have overcome this limitation. Moreover, the attachment style, experienced with the attachment figure since birth, may change during the life cycle. The experiences with other significant and the new adaptations to the demands posed by the various stages of life exert their influence acting as corrective. It is possible that, in the advanced stages of dementia, these adaptations could be lost due to the deterioration of capability of access to the meaning of emotional states. The comprehension of the attachment style of the PWD is of key importance, so that caregivers can interpret and respond to specific modalities of the PWD to ask for closeness and protection [37].

A limitation of this study is the exclusion of men. This is because women are 71.6% of patients with dementia living in nursing homes of the Canton Ticino, as reported by the Department of Health and Sociality of the Canton Ticino (source: Statistica intra-muros, SOMED, Dipartimento della sanità e della socialità, Unità statistiche sanitarie, Bellinzona). The authors have chosen to exclude men in order to have the most homogeneous sample in the time frame of the study, but further research is needed in order to demonstrate the feasibility of DT in men. The need for attachment and the ability to provide assistance are linked to the innate drive to give security and comfort to an individual who presents physiognomic characteristics of fragility and vulnerability (small nose, high forehead, soft skin). These characteristics activate caregiving behaviours and oxytocin increase, supporting the caregiving activity: this is not about gender but about characteristics belonging to all humankind [38]. Physiological parameters will always be monitored during the interventions (first or 30th session) both for the experimental (doll) and active control groups (cube), but we will not collect the basal stress levels prior to any interference of the intervention (cube or doll).

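### On its most natural reading, the supplementary regression of NPI-NH change adjusts for physiological outcomes affected by treatment, so its group term does not estimate the doll's effect

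*Protocol article*

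**What the plan says.** The Statistical analyses section of the Protocol article tests the primary outcomes by ANCOVA, with baseline NPI-NH and psychotropic medication as covariates. It then adds a multiple regression that asks how much of the NPI-NH change is attributable to arm "after controlling for baseline NPI-NH and biological parameters, a multiple regression analysis will be performed". It does not say which physiological readings enter. Two sentences earlier, however, it describes the same variables as "biological parameters (decreased, influent, or increased) of each patient at the baseline versus the post intervention", which is a direction-of-change coding.

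Under Primary outcomes, the Physiological outcomes section states: "We have planned to monitor three physiological outcomes: blood pressure (systolic and diastolic), heart rate and salivary cortisol level". Readings are taken "immediately before the treatment and 15 min after the end of treatment at the first and the 30th session of DTI or SI". The Primary goal section expects improvement in these stress indices, which it ties to BPSD, "in terms of a decrease in the following parameters: salivary cortisol, blood pressure (systolic and diastolic) and heart rate". The Physiological outcomes section expects the arms to differ on blood pressure, heart rate and cortisol.

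**The concern.** A covariate that treatment has already changed does not behave like a baseline covariate. If the doll lowers stress markers and those markers move with behaviour, holding the markers fixed takes out the part of the behavioural benefit that runs through, or alongside, reduced stress. The group coefficient then answers a different question: how do the arms differ among patients with the same physiological response? The article itself expects both conditions, since treatment is to move the markers and the markers are said to be linked to BPSD.

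The regression is not labelled exploratory or mechanistic, and one 0.05 threshold is applied to all comparisons. A positive ANCOVA could therefore be reported beside a weak or null regression on the same outcome, with no stated rule for reading the two together.

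**Working it through.** **Inputs from the Protocol article (Sample size).** f = 0.25, alpha 0.05, power 0.8, N = 128 (64 per arm), one covariate (baseline NPI-NH). For two equal arms d = 2f = 0.5 SD.

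**Inputs the documents do not give (assumed).** a is the doll's effect on the marker, in within-arm SD and in the direction of benefit. r is the within-arm correlation of the marker with NPI-NH improvement. Each is varied from 0.2 to 0.5, with zero as reference. One marker stands in for the set.

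**Step 1: the plan's own figure.** The noncentrality is f²N = 0.0625 × 128 = 8, with 1 and 125 degrees of freedom. Power is 0.801, and 128 is the smallest N that reaches 0.80. The stated sample size is reproduced.

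**Step 2: which values enter the regression.** The article describes two derived forms of these variables. One is the direction of change from baseline to post intervention (Statistical analyses). The other is the ratio of the pre-session to the 15-minute reading at sessions 1 and 30 (Physiological outcomes). Both contain at least one reading taken after exposure to the doll or cube. Only the raw reading just before session 1 precedes exposure.

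**Step 3: effect of adjusting.** With unit within-arm variances:

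- adjusted group effect = d − r·a
- share removed = r·a / d
- variance of the group estimate = (4/N)(1 − r²)(1 + a²/4)
- power from the noncentral t with 124 degrees of freedom

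Low end, a = r = 0.2: effect 0.5 − 0.04 = 0.46; SE = √(0.03125 × 0.96 × 1.01) = 0.174; noncentrality 2.64; power 0.75.

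High end, a = r = 0.5: effect 0.5 − 0.25 = 0.25; SE = √(0.03125 × 0.75 × 1.0625) = 0.158; noncentrality 1.58; power 0.35.

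| a | r | Adjusted effect (SD) | Removed | Power |
|---|---|---|---|---|
| 0 | 0 | 0.50 | 0% | 0.80 |
| 0 | 0.3 | 0.50 | 0% | 0.84 |
| 0.5 | 0 | 0.50 | 0% | 0.78 |
| 0.2 | 0.2 | 0.46 | 8% | 0.75 |
| 0.3 | 0.3 | 0.41 | 18% | 0.67 |
| 0.5 | 0.3 | 0.35 | 30% | 0.52 |
| 0.5 | 0.5 | 0.25 | 50% | 0.35 |

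**Step 4: simulation (4,000 trials per setting).** At a = 0.5, r = 0.3 a continuous marker gives a mean estimate of 0.352 and power 0.51, in line with the formula. A three-category marker, as the article describes, gives 0.386 and 0.58. At a = r = 0.5 the figures are 0.251 and 0.35 for the continuous marker, and 0.305 and 0.45 for three categories. Coarse coding softens the loss but does not remove it.

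**The case against.** The best counter-argument is grammatical. The word baseline in the regression sentence may govern both NPI-NH and the biological parameters. A pre-exposure value does exist: readings are scheduled just before session 1, participants must have had no earlier doll therapy, and the nurse brings the object in only after the patient is seated. Adjusting for that reading alone would remove none of the effect. This stands as a possible reading. It is the weaker one, because the same section codes these variables as change and never mentions a pre-session-1 value as a covariate.

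It is also fair to say that this regression is not the test of the primary outcomes, that the trial was not powered on it, and that both a and r are assumed. All of that stands and limits the point to a supplementary model.

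Three stronger readings are tempting but not supported:

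- **That the primary efficacy test is compromised.** The ANCOVA does not list the physiological variables as covariates.
- **That no usable pre-exposure reading exists**, because the Discussion says "we will not collect the basal stress levels prior to any interference of the intervention (cube or doll". The measurement schedule in Physiological outcomes still provides a reading before first exposure.
- **That the ANCOVA has the same fault through its medication covariates.** The Background notes of doll therapy that "A significant reduction of antipsychotic drug dosage (e.g. haloperidol) has also been reported [11", and the Other variables section lists "total number and relative dosages of psychopharmacological therapies for behavioural and psychiatric symptoms" without a time point. But that section refers to Table 3 for assessment times, and the table is not reproduced in the available text. Which visit's value enters is also a detail commonly left to the analysis plan. Silence here does not show that post-baseline values are used.

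**Conclusion.** The point holds for the supplementary regression, on the most natural reading of the Statistical analyses section. As described, the model controls for variables that are themselves trial outcomes expected to respond to the doll. Its group coefficient and its variance explained by group therefore do not estimate the effect of Doll Therapy on NPI-NH.

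The size cannot be derived from the documents. For a and r each between 0.2 and 0.5, between 8% and 50% of a 0.5 SD effect is removed. With a or r at zero nothing is removed, although that would contradict the article's own expectations. Attenuation is not guaranteed either: unmeasured causes shared by stress and behaviour can bias the adjusted coefficient in either direction, so it is not a clean direct effect. The ANCOVA of the primary outcomes and the sample size of 128 are untouched.

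**What to change.** State that the regression estimating the group effect on NPI-NH change uses pre-exposure covariates only: baseline NPI-NH and, if wanted, the physiological readings taken immediately before session 1. Label any model containing change categories, post-session readings, session ratios or session-30 values as an exploratory mediation analysis that makes no efficacy claim. Say that the ANCOVA carries the efficacy conclusion if the two differ.

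If baseline physiological values were always intended, one clarifying sentence is enough. The cost is wording only: no new data, no change to visits and no change to sample size. The wording should be settled before outcomes are analysed by arm.
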